### Phase 2—Sub-study: qualitative interviews

Face-to-face interviews with ten participants in the UK and ten participants in Uganda will be conducted post-intervention (immediately after the final intervention session, and at the 6-month follow-up) to aid in the assessment of feasibility and to clarify potential causal mechanisms of the intervention. Individuals will be sampled purposively from both conditions (interventions and standard of care) to ensure that a range of participant characteristics (e.g. age, gender, level of HIV sharing) are represented.

#### Procedure

**Phase 1**

***Sampling and identification***

Young people with PAH meeting the inclusion criteria will be identified by clinicians and representatives of support organisations with an attempt to sample those with a range of levels of onward HIV disclosure and with a range of demographic characteristics. Friends, family and partners of young people with PAH will be identified by the young person with PAH. Professionals working with young people with PAH will be identified by the research team, attempting to sample across a range of clinics and support organisations.

***Approach and provision of study information***

Young people identified will be informed about the study verbally by a named clinician or support organisation representative by phone or at their next clinic/support organisation appointment. If they are informed by phone and are interested in the study, they will be asked permission for their professional to pass on their contact details to the study coordinator. The study coordinator will contact the young person to arrange a time to meet and to go through the participant information sheet. If the young person is informed at their next clinic/support organisation appointment, they will be given the participant information sheet by the professional who will either go through this with them or ask the study coordinator to do this, if they are available. If the young person is interested in taking part, having gone through the participant information sheet with the professional, their details will be passed on to the study coordinator.

Young people will be asked whether they can identify any friends, family members or regular partners who they think might like to take part in the study. The young person will be asked to discuss the project with them and to provide the study coordinator’s details. If friends, family or partners are interested in finding out more about the study, they will be asked to contact the study coordinator by phone. If they are interested, they will arrange a time to meet the study coordinator to go through the participant information sheet. For professionals working with young people with PAH, the study coordinator will inform them about the study by phone. If they are interested, they will arrange a time to meet the study coordinator to go through the participant information sheet.

***Consent and participation***

Written informed consent will be sought by the study coordinator or a member of the clinical team. Participants will be asked to offer their consent for all elements of this phase of the study, despite the fact that they may not be asked to take part in all activities. The right to withdraw will be stressed. One copy of the signed consent form will be given to the participant and one will be kept by the study coordinator to file in the central study register. The participant will be enrolled and then they will participate in the study. Travel expenses will be paid and participant payments will be made to non-professional participants and receipts will be kept by the study coordinator.

**Phase 2: main study**

***Sampling, identification, screening and randomisation***

A sampling frame will be constructed for each site by a named clinician applying the inclusion and exclusion criteria to their clinic population. A record of young people who are not eligible will be kept in a site study log to ensure that these individuals are not screened or approached in the future. Anonymised details of those not eligible (with reasons) will be passed to the study coordinator to record in the central study register to enable a study flow diagram to be compiled. The details of those eligible to participate will be provided to the study coordinator. Simple random sampling (without replacement) will be used by the study coordinator to identify which young people are approached to take part in the study from among those eligible across the sites in the country (using Research Randomizer: https://www.randomizer.org/).

***Approach and provision of study information***

If young people are eligible and randomly selected to be approached, the study coordinator will inform a named clinician at each site. The young person will be informed about the study verbally by the named clinician by phone, text or email, or at their next clinic appointment. If the young person expresses an interest in the study, they will be given further information by either the clinician or the study coordinator (the latter after permission for the clinician to pass on their contact details to the study coordinator has been sought). If the study coordinator is the person providing further information, the study coordinator will contact the young person to arrange a time to meet and to go through the participant information sheet. If the clinician is the person providing further information, the young person will be given the participant information sheet by the clinician who will go through this with them. If the young person is interested in taking part, having gone through the participant information sheet with the clinician, their details will be passed on to the study coordinator. If potential participants are not interested in taking part, this will be recorded in the site study log by the named clinician and anonymised information (with the reason for refusal) will be provided to the study coordinator to record in the central study register. This will help to determine the study response rate.

***Consent***

Written informed consent will be sought by the clinician or the study coordinator in each country. Consent documents will be translated into Luganda in Uganda, with the participants in Uganda having the choice between English or Luganda documents. Young people will be asked to offer their consent for both the main study and the sub-study at the same time, despite the fact that only a proportion of those taking part in the main study will be asked to take part in the sub-study. Consent will be sought for access to clinic data. Consent will also be sought for young people to be contacted before their follow-up assessment as a reminder and after this assessment if they have not attended. One copy of the signed consent form will be given to the participant, one for the clinical notes, and one will be kept by the study coordinator to file in the participant’s personal study register.

***Enrolment, randomisation (both conditions) and baseline assessments (standard-of-care condition only)***

The study coordinator will arrange the enrolment visit at the end of the consent process if the study coordinator has taken consent. If the clinician has taken consent, the study coordinator will contact the participant to arrange the enrolment visit. If the study coordinator and the participant are able to carry out the enrolment process at the same time as consent is obtained, this will be offered. At the enrolment visit, the participant will be enrolled into the study and given a study ID. Personal information will be recorded by the study coordinator in the participant’s personal study register (name, contact details, etc.) and non-identifiable information will be recorded in the central study register (study ID, date of enrolment, etc.).

Stratified block random allocation to condition by country/site (UK inner city NHS clinics and Uganda) will be used. There will be 12 blocks of either 15 or 16 participants per block (six blocks in Uganda, five blocks in London and one block in Birmingham). Computer-generated randomisation will be used using the Research Randomizer. The randomisation will be carried out by the study PI in the UK and the site PI in Uganda. Allocation will be concealed from the study coordinator in each country through the use of sequentially numbered opaque envelopes. The study coordinator will inform the participant which condition that they have been allocated to.

If the participant is in the standard-of-care condition, the baseline assessment will then be administered by the study coordinator, who will also record clinical information from the clinical notes or database for participants in this condition. Travel expenses will be paid to participants in both the intervention and the standard-of-care conditions if any have been incurred and a receipt will be kept.

***Baseline assessment (intervention condition) and intervention***

If the participant has been allocated to the intervention condition, their details will be passed to the intervention therapists, who will liaise with the study coordinator and participant about the timetabling of the baseline assessment and intervention sessions. The participant will be asked for their preference about when they would like intervention sessions to take place. The therapists will also explore any concerns that the participant has about the intervention. The baseline assessment will be administered by the study coordinator immediately prior to the first intervention session. The study coordinator will also record clinical information from the clinical notes or database.

All four intervention sessions will take place within a month time period. It is hoped that intervention participants will attend all four sessions, but they will be allowed to move on the next session if they have missed a previous one. All intervention sessions will be taped. Session attendance will be recorded by the therapists. A random selection of 10% of the sessions will be reviewed by one from the research team for fidelity to the intervention (using an intervention checklist), and feedback will be offered to the therapists based on this review (as well as problem-solving supervision). Travel expenses will be paid to participants by the therapists if any have been incurred and a receipt will be kept and passed on to the study coordinator. Participants will be remunerated for each intervention session.

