### Intervention condition

The intervention condition will consist of four sessions (90 min per session) delivered in a mixed group/individual format (three group sessions including seven or eight participants/one individual session); professionally led (therapist one); mixed gender; face-to-face; with peer mentor involvement (therapist two) and follow-up support. These features were preferred by clinic attendees in survey of 57 young people with PAH in the UK [53] and were seen as feasible in a second survey of 16 professionals working with this population in the UK [54].

The intervention will aim to develop motivation and skills for HIV status sharing, increase HIV status sharing self-efficacy, decrease anxiety about HIV sharing and increase satisfaction with HIV status sharing decision-making. Motivational interviewing (MI) and Cognitive behavioural therapy (CBT) will guide the intervention. The intervention will be delivered by two therapists in each country. One will be a health professional (not a mental health specialist). The other will be a peer worker.

The content of the intervention is based on models of HIV disclosure decision-making and HIV disclosure anxiety [55–58] and existing evidence of HIV status-sharing correlates, barriers and facilitators [25, 28, 59]. In particular, disclosure attitudes, normative beliefs, self-efficacy, planning and support are argued to be important proximal determinants of HIV status sharing. These factors are suggested to be influenced by more distal factors: personal values and HIV stigma.

The content of specific sessions will be as follows:

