***Follow-up measurement***

This will occur 6 months after the baseline measures have been completed for both participants in the intervention condition and the standard-of-care condition and will be conducted by the study coordinator. We will use participant reminders and prompts (provided by the study coordinator) to minimise attrition. Participants will be contacted 1 month and 1 week before the second/third study visit is due (by phone/SMS), and attempts will be made to arrange the location and time of this visit. Participants will be reimbursed for their time and for any travel expenses incurred. Receipts will be kept by the study coordinator.

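### Baseline is measured after allocation is disclosed, and later in the intervention arm than in standard care, so baseline measures and early losses differ by arm

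*Protocol article*

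**What the plan says.** The order of events is set out in the Phase 2 main study procedure of the protocol article.

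- **Disclosure.** At enrolment and randomisation, "The study coordinator will inform the participant which condition that they have been allocated to".
- **Standard care.** "If the participant is in the standard-of-care condition, the baseline assessment will then be administered by the study coordinator". The word *then*, with a section heading that limits these baseline assessments to standard care, implies the same visit, although the text does not say so outright.
- **Intervention.** Details go to the therapists, "who will liaise with the study coordinator and participant about the timetabling of the baseline assessment and intervention sessions". Before that baseline, "The therapists will also explore any concerns that the participant has about the intervention". Then: "The baseline assessment will be administered by the study coordinator immediately prior to the first intervention session". No upper limit is set on the interval from allocation.
- **Group format.** The intervention has "three group sessions including seven or eight participants/one individual session", so session 1 needs a group to be assembled. On allocation, "There will be 12 blocks of either 15 or 16 participants per block", which yields about one group of seven or eight per block.
- **Follow-up.** "This will occur 6 months after the baseline measures have been completed", in both arms.

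Under Primary outcome measure, recruitment and retention are to be calculated by site and by condition. No denominator for retention is given.

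**The concern.** A baseline should be untouched by the allocation. Here it follows disclosure in both arms, and in one arm it also follows therapist contact and a wait. Three things are at stake.

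1. **Self-report.** Recent sharing, disclosure intention, self-efficacy, decisional conflict and well-being are reported by a participant who knows the arm to a coordinator who knows it too. Expectation or disappointment can shift the answers, and the conditions for this differ by arm. Opaque envelopes protect the assignment, not a measurement taken after it is revealed.
2. **One-sided early loss.** An intervention participant who drops out between allocation and session 1 has no questionnaire baseline. No follow-up date can be set either, because the six months run from baseline. Standard care has essentially no such gap. Retention by condition is part of the primary outcome, and retention is among the criteria for moving to a full trial.
3. **Shifted recall windows.** New sharing is counted over the last six months. Sharing between allocation and session 1 falls in the baseline window in the intervention arm. The corresponding weeks after allocation fall in the follow-up window in standard care.

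**Working it through.** **The plan's own figures first.** The inputs are 94 per condition and 47 per condition per country (Sample), 68% anticipated retention, and a half-width of 9.5 points for n = 94 per country (Data management and analysis, Phase 2 main study).

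- Retained per condition: 94 × 0.68 = 63.9, which agrees with the target of 64.
- Retained per arm per country: 47 × 0.68 = 32.0, which agrees with 32.
- Half-width per country: 1.96 × √(0.68 × 0.32 / 94) = 9.4 points, close to the stated 9.5.
- Half-width for one arm in one country: 1.96 × √(0.68 × 0.32 / 47) = 13.3 points.

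**Effect of the denominator.** Let L be the share of the intervention arm lost between allocation and session 1. L is not in the protocol; 5, 10 and 15% are assumptions. Suppose 68% of all randomised participants are retained in both arms, but retention is divided by those with a baseline.

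- Intervention arm: 0.68 / (1 − L).
- Country, both arms: (94 × 0.68) / (47 + 47 × (1 − L)) = 63.92 / (47 + 47 × (1 − L)).

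| L (assumed) | Intervention arm reads | Country denominator | Country reads | Country shift |
|---|---|---|---|---|
| 5% | 71.6% | 91.65 | 69.7% | 1.7 points |
| 10% | 75.6% | 89.30 | 71.6% | 3.6 points |
| 15% | 80.0% | 86.95 | 73.5% | 5.5 points |

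Standard care stays at 68% throughout. Within the arm, the shifts of 3.6, 7.6 and 12.0 points are to be set against 13.3. The country shifts are to be set against 9.5.

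The reverse case: if 68% of those with a baseline are retained, intervention retention from randomisation is 0.68 × (1 − L) = 64.6, 61.2 or 57.8%. That is 30.4, 28.8 or 27.2 of 47, against 32.0 in standard care.

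**Length of the wait.** The protocol does not state it. For illustration, assume even accrual of 94 per country, over about 12 months in the UK (August 2020 to July 2021) and 10 months in Uganda (October 2020 to July 2021), with groups starting when a block of 15 or 16 fills.

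- UK pooled: 94 / 12 = 7.83 per month. A block fills in 1.9 to 2.0 months, and the mean wait is (block size − 1) / 2 / 7.83 = 0.9 to 1.0 months.
- Uganda: 94 / 10 = 9.4 per month. A block fills in 1.6 to 1.7 months, and the mean wait is 0.7 to 0.8 months.
- London taken alone: five blocks in 12 months gives 12 / 5 = 2.4 months per block, so a mean wait of about 1.2 months.

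A one-month wait puts the intervention follow-up at 7 months from randomisation, against about 6 in standard care. From baseline it is 6 months in both arms.

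**The case against.** Taking baseline at session 1 has a rationale: every intervention participant's six-month window then covers the whole intervention and its peer follow-up support. This explains the timing, but it does not require the baseline to come after disclosure.

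A reader might infer more than the text supports.

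- **That early intervention losses drop out of the primary outcome.** The follow-up visit is timed from baseline, but no passage makes baseline the denominator for retention. The figures (94 per condition retaining 64; n = 94 per country) point to the full sample. The analysis section also aims for follow-up of everyone enrolled, whatever their involvement in the intervention. An article may leave the exact denominator to a fuller document.
- **That follow-up is of unequal length.** Counted from baseline it is six months in both arms, and the recall windows are equally long. Only their position relative to randomisation differs.
- **That the bias rivals the stated precision of 9.5 points.** That half-width is for a country with both arms pooled. The 7.6-point shift at 10% loss is within one arm, where the half-width is 13.3 points. The like-for-like country shift is 3.6 points.
- **That nothing is known about early losses.** Consent covers clinic data, and personal details are recorded at enrolment. What is missing is the questionnaire baseline.
- **That waits run to many months, for instance in Birmingham with its single block.** No rule ties group starts to block completion, and accrual by site is not given.

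It is also fair that the trial is a feasibility study, that efficacy is only one of several progression criteria, and that the sharing hypothesis compares rates at follow-up without specifying a baseline-adjusted model. These points limit the severity. They leave the order of disclosure and baseline, and the one-sided gap, as they are.

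**Conclusion.** The concern holds. The document itself fixes a baseline that follows disclosure in both arms and comes at different points in each. Three consequences follow directly: self-reported baselines open to arm-dependent influence, questionnaire baselines and follow-up dates missing for early intervention losses, and post-allocation sharing assigned to different windows by arm. Their direction and size cannot be derived from the protocol.

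The retention figures are conditional. They apply only if the denominator is participants with a baseline, and only for the assumed losses. On that footing, the distortion is about 4 to 12 points in the intervention arm and about 2 to 6 points per country, each smaller than the matching half-width. The waiting times rest on assumed accrual and grouping rules.

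This should be fixed. It touches how a primary outcome is compared between arms, and the baseline order cannot be repaired in analysis. It does not invalidate the feasibility aims.

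**What to change.** 1. Give the baseline questionnaires to every participant at the enrolment visit, before the envelope is opened.
2. State that retention by condition is calculated with all randomised participants as the denominator.
3. Report, by arm, the interval from allocation to session 1 (for standard care, to the corresponding point) and the number lost in it.

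The coordinator, the instruments, the visit and the sample size of 188 stay the same. The cost is a re-ordered procedure and revised wording.

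Because follow-up is tied to baseline, moving the baseline also moves the follow-up clock, so the protocol should restate it. Dating follow-up from the same point in both arms is preferable where the wait for a group is short. The downside is that, if a group starts late, less time after the intervention falls within the six months. Randomising in batches, once enough participants for a block have consented, would limit this. It makes both arms wait, however, and sits awkwardly with the offer to enrol at the consent visit, so it is optional.

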***Post-intervention measurement***

This will take place for the intervention group only. It will take place at the end of the final session. This will be carried out by the study coordinator. Travel expenses will be paid if any have been incurred and participant payments made, and receipts will be kept by the study coordinator.

***Follow-up measurement***

This will occur 6 months after the baseline measures have been completed for both participants in the intervention condition and the standard-of-care condition and will be conducted by the study coordinator. We will use participant reminders and prompts (provided by the study coordinator) to minimise attrition. Participants will be contacted 1 month and 1 week before the second/third study visit is due (by phone/SMS), and attempts will be made to arrange the location and time of this visit. Participants will be reimbursed for their time and for any travel expenses incurred. Receipts will be kept by the study coordinator.

***After the follow-up assessment***

The following activities will take place after the follow-up assessment (by the study coordinator).
Attempts to track participants if they have not attended their follow-up visit (by phone/SMS)Obtaining clinic data

**Phase 2: sub-study**

***Sampling and identification***

For the sub-study, participants in both conditions will be identified by the study coordinator to ensure that a range of characteristics are represented (e.g. age, location and sex) at each interview time point (post-intervention and follow-up).

***Approach***

The study coordinator will contact young people who have been identified to ask whether they would like to participate in the sub-study. If they are willing to participate, this will be recorded in their personal study register and the central study register. The study coordinator will arrange a time and location for the interview with the participant. If potential participants are not interested in taking part, this will be recorded in anonymised form (with the reason for refusal) in the central study register. This will help to determine the sub-study response rate.

